**Fig. 1 Fig1:**
[figure not shown]
SPIRIT figure of the schedule for enrolment, intervention implementation, and assessment time points

#### Data management

Hard copies of data will be kept confidential and stored securely in a locked cabinet within the School of Nursing and Midwifery, Queen’s University Belfast. Soft copies of data obtained throughout the study will be stored on the Queen’s University Belfast Cloud Storage (Q) Drive.

### Statistics and data analysis

#### Quantitative analysis

Quantitative data analysis will be conducted using SPSS V.24. Descriptive statistics will be used to report on baseline demographic, clinical data, and program usability. Categorical data will be presented as frequencies and percentages, whilst continuous data is presented as means and standard deviations. Numerical data will be analysed using SPSS V.24. Repeated measures ANOVA will be used to assess the preliminary efficacy between groups across three time points for physical activity, clinical indices, and psychosocial status.

As a feasibility randomised controlled trial, and therefore not statistically powered, results will be interpreted with caution. Recruitment and retention rates will be reported on and presented using the CONSORT flow diagram [21].

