**Methods:**

A randomised wait-list controlled trial will be conducted with a sample of 30 male taxi drivers to establish feasibility, including recruitment, engagement, and retention rates. Program usability and participant satisfaction will be assessed by a survey completed by all participants at 3 months after allocation. Additionally, an in-depth qualitative process evaluation to explore acceptability of the intervention will be conducted with a subset of participants by semi-structured telephone interviews. Preliminary efficacy of ManGuard for improving key CVD-related outcomes will be assessed, including biomarkers (total cholesterol, HDL cholesterol, LDL cholesterol, triglycerides, and total/HDL cholesterol ratio), blood pressure, anthropometry (body mass index, body fat percentage, and waist circumference), physical activity (accelerometery, and self-report) and psychosocial status (health-related quality of life, self-efficacy, and social support). Outcomes will be assessed at baseline, 7 weeks, and 3 months after group allocation. The wait-list control group will be offered access to the intervention at the completion of data collection.

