### Participants

#### Eligibility criteria for participants

Adult males (≥ 18 years)Working part-time or full-time as a taxi driver in Northern IrelandHaving access to the internet and a smartphone that allows for the downloading of mobile applications.

As this is a feasibility randomised controlled trial, no formal power calculation will be completed to determine sample size. Recommendations on the appropriate sample size for pilot and feasibility studies vary greatly, with sample sizes ranging between 24 and 50 participants [57]. We have chosen a sample size of 30 for this study, as recommended by the National Institute for Health Research (NIHR) in the UK [30].

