### Intervention

The intervention is an eHealth program (ManGuard) that aims to reduce CVD risk in male taxi drivers. ManGuard was developed utilising a co-design approach, involving an ongoing collaboration between the research team, a computer scientist, and end-users (taxi drivers). Utilising co-design with an iterative approach is crucial for the success of an eHealth intervention [64]. First, an online survey was disseminated to gain an insight into life as a taxi driver in Northern Ireland and to guide the initial development of ManGuard. Utilising the iterative process between a Project Advisory Group (PAG) and focus groups with end-users, low-fidelity prototypes for the program and materials that would make up the ‘content’ where refined. The inclusion of behaviour change theory in the development of health interventions is reported as an essential component for improving their effectiveness [59]. The Behaviour Change Wheel (BCW) was incorporated throughout the development of ManGuard, providing a pragmatic framework and ensuring the incorporation of theory throughout [40]. Guided by the BCW worksheets [42], physical activity was identified as the behaviour anticipated to produce the greatest reduction in CVD risk in male taxi drivers. This was due to the long periods of sedentary time associated with the occupation, the likelihood of male taxi drivers changing the behaviour, the impact that physical inactivity has on other CVD-related behaviours, and the ease of measurement in a clinical trial. Next, it was specified that male taxi drivers should aim to complete greater levels of physical activity daily, in any setting, and with whomever they wish.

The next step in the process was to ensure the intervention was grounded in behaviour change theory, beginning with the conduction of a behavioural analysis. Doing so uncovers what needs modified at the individual level for successful change to occur. Next, the outcomes of the analysis were mapped to intervention functions deemed appropriate for facilitating the necessary change. Lastly, behaviour change techniques (BCTs) that could successfully deliver the intervention functions were identified using the BCT taxonomy [41], and through an assessment of BCTs utilised in previous eHealth interventions targeting male only participants [39]. ManGuard will be delivered as an application (app), accessible through handheld devices including mobile phones and tablets.

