#### Clinical indices

Though not powered to detect clinically significant change, the following CVD-related outcomes will be assessed to determine preliminary efficacy of ManGuard, and feasibility of each for inclusion in a definitive trial:

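### Repeated measures ANOVA is the only stated way to judge preliminary efficacy on at least 16 outcomes in 30 men; between-group differences with confidence intervals would serve the next trial better

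*Protocol article*

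**What the plan says.** The protocol article's Quantitative analysis section gives one sentence on how efficacy will be judged: "Repeated measures ANOVA will be used to assess the preliminary efficacy between groups across three time points for physical activity, clinical indices, and psychosocial status". The only other numerical summaries there are frequencies, percentages, means and standard deviations.

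On design, "We have chosen a sample size of 30 for this study", and "no formal power calculation will be completed to determine sample size". On visits, "Outcomes will be assessed at baseline, 7 weeks, and 3 months after group allocation". Blocked randomisation is meant to give equal groups, so about 15 men per arm.

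Two caveats are given. The Clinical indices section says "Though not powered to detect clinically significant change, the following CVD-related outcomes will be assessed to determine preliminary efficacy of ManGuard", and adds that the feasibility of each outcome for a definitive trial will be judged. The Quantitative analysis section says "As a feasibility randomised controlled trial, and therefore not statistically powered, results will be interpreted with caution".

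Research aims and objectives makes the efficacy outcomes secondary to the feasibility measures. Progression criteria uses recruitment, retention and acceptability only. The Intervention section explains the choice of target behaviour: "physical activity was identified as the behaviour anticipated to produce the greatest reduction in CVD risk in male taxi drivers". No section ranks the efficacy outcomes.

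**The concern.** The study is meant to inform a fully powered trial. For each candidate outcome, the designers of that trial will want to know how far apart the groups were, at which follow-up visit, and with what uncertainty. A two-group, three-visit ANOVA does not return this.

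- The group term averages the pre-treatment visit in with the two follow-up visits.
- The group-by-time term is a 2-degree-of-freedom test that says the difference between groups is not constant over visits, without saying where or in which direction.

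Repeating the test over 16 or more outcomes also gives a substantial chance that something reaches nominal significance when nothing has changed. If that result becomes the headline, it could colour the published efficacy message or the choice of outcome for the definitive trial.

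**Working it through.** **1. Number of outcomes** (sections CVD biomarkers to Psychosocial status)

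| Domain | Count |
|---|---|
| Lipids (total, HDL, LDL, triglycerides, total/HDL ratio) | 5 |
| Systolic and diastolic blood pressure | 2 |
| BMI, body fat, waist | 3 |
| Accelerometer and IPAQ-SF | 2 |
| SF-12 physical and mental | 2 |
| GSE | 1 |
| MSPSS | 1 |
| **Total** | **16** |

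Glucose is named in the objectives but not in the biomarker list; with it the count is 17. Several accelerometer summaries or MSPSS subscales would add more, so 16 is a minimum.

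**2. What the omnibus terms can show**

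Let the between-group differences at baseline, 7 weeks and 3 months be (δ1, δ2, δ3), with mean δ̄ and n = 15 per arm. The interaction sum of squares is (n/2) × Σ(δt − δ̄)².

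- Difference at 7 weeks only, (0, d, 0): Σ = d²(1/9 + 4/9 + 1/9) = 2d²/3, so SS = 7.5 × 2d²/3 = 5d².
- Difference at 3 months only, (0, 0, d): 5d².
- Difference at both follow-up visits, (0, d, d): Σ = d²(4/9 + 1/9 + 1/9) = 2d²/3, so SS = 5d².
- Chance baseline imbalance that disappears, (d, 0, 0): 5d².
- Reversing the sign of d changes none of these.

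The test statistic has the same numerator for an early effect, a late effect, a sustained effect and a baseline imbalance. The group term, for a sustained effect d, estimates (0 + d + d)/3 = 2d/3, because baseline is averaged in.

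**3. Chance positives with no true effect**

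The document states no significance level, error rate or power, so there is no figure of its own to reproduce. Assumptions: 5% per F test, 15 per arm, no dropout, correlation 0.7 between visits within a person, 16 outcomes, 4,000 simulated trials per setting.

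Check under independence, one term per outcome: 1 − 0.95^16 = 0.560 (17 outcomes: 1 − 0.95^17 = 0.582). Expected false positives: 16 × 0.05 = 0.8.

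| Common correlation between outcomes | Any group-by-time term p < 0.05 | Any group or group-by-time term p < 0.05 |
|---|---|---|
| 0 | 56% | 81% |
| 0.3 | 49% | 73% |
| 0.5 | 40% | 64% |
| 0.7 | 29% | 48% |
| 0.8 | 22% | 38% |

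With higher correlation inside domains (0.5 to 0.8) than between them (0.1 to 0.3), the group-by-time figure is 39% to 52% and the either-term figure 62% to 76%. Simulation error is about 0.8 percentage points (√(0.4 × 0.6/4000) = 0.008), so repeat runs move these values by a point or two.

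**4. What an estimate would show instead**

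For one baseline-adjusted difference at one visit, with 15 per arm, no dropout and baseline correlation r, the 95% half-width in SD units is t(0.975, 27) × √[(2/15)(1 − r²)], where t = 2.052.

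- r = 0.7: 2.052 × √(0.1333 × 0.51) = 0.54 SD.
- r = 0.5: 2.052 × √(0.1333 × 0.75) = 0.65 SD.

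An interval that wide makes the imprecision of any single result visible; a p-value does not.

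**The case against.** The strongest objection is that this is exploratory work, openly labelled as such, described in a condensed article. Efficacy is secondary, twice declared unpowered, and to be read with caution. That caution applies to all results; low power also makes a nominally significant result less trustworthy and tends to inflate its size, so the caveat is not confined to null findings. All of this stands, and it limits the severity.

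Four stronger readings may tempt a reader. The document does not support them.

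- *A false positive is likely.* For the group-by-time term alone the chance passes 50% only when outcomes are close to independent. That is hard to believe for five lipid measures, one of them a ratio of two others, or for BMI, waist and body fat. The larger figures require the group term to count as well, and the reference to three time points reads more naturally as group-by-time.
- *The plan is defective because it omits the significance level, the deciding term, a hierarchy and multiplicity control.* An article may leave these to the full protocol or analysis plan, neither of which is shown.
- *Anything below 0.05 will be declared efficacy and carried forward.* No threshold and no such rule appears.
- *A chance result could send the trial forward.* Progression criteria contains no efficacy result.

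It can also be said that arm means and standard deviations may be tabulated by visit, so a reader could form the differences. That helps only in part: the text does not clearly promise these summaries after baseline, and they do not give a baseline-adjusted interval.

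The choice of instrument remains open to criticism. The article itself commits to ANOVA as the means of judging efficacy, so this is a stated choice and not a silence.

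**Conclusion.** The point holds as a minor one. On at least 16 outcomes in 30 men, the only stated basis for preliminary efficacy is an omnibus test that gives neither the size nor the visit of a between-group difference. The chance-positive figures (about 40% to 50% at correlations of 0.3 to 0.5, one term per outcome) rest on an assumed 5% level, an assumed visit correlation of 0.7 and complete data. They are several times 5% throughout the range examined, but they illustrate the problem and are not a property that the document states. What is at risk is the efficacy message and the choice of outcome for the definitive trial.

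**What to change.** Replace the ANOVA sentence in the Quantitative analysis section with wording such as:

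> Efficacy outcomes are exploratory. For each outcome the between-group difference at 7 weeks and at 3 months will be reported with a 95% confidence interval. No claim of efficacy will rest on a single interval that excludes zero.

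Optionally, name one lead outcome and one visit before the data are seen. Accelerometer-measured physical activity is a natural candidate because physical activity is the target behaviour, but the outcome and the visit are the team's choice.

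The cost is wording only: no new data, visits or participants. The team gives up reporting individual significant results from a 30-man trial.

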### eHealth interventions for behaviour change

eHealth offers a means of tailoring interventions to meet the needs of end-users and has the potential to improve intervention uptake, adherence, and success [65]. Defined as “the use of technology to improve health, well-being and healthcare” [65], eHealth provides participants with an easily accessible and easy to use intervention [45]. The ease of access and use may be of benefit to taxi drivers, presenting as a hard-to-reach group due to the remote nature of the occupation. A recent systematic review and meta-analysis reported the success of eHealth interventions in promoting behaviour change among those living with NCDs [18]. Another recent systematic review and meta-analysis by us found similar findings for the reduction in CVD risk in men, with improvements in body weight, body mass index (BMI), waist circumference and blood pressure observed as a result of eHealth interventions [39].

However, weaknesses of eHealth interventions include poor adherence and high rates of attrition [33, 35]. To counter this, it is important that consideration is given to the needs of the end-users, iteratively developed, grounded in behaviour change theory and rigorously evaluated prior to the dissemination of findings [46, 50, 65].

The IDEAS (Integrate, Design, Assess, and Share) framework has been proposed for the design, development, and evaluation of eHealth interventions [46], and was utilised for the development of ManGuard. This 10-phase framework draws on the strengths of several approaches for eHealth interventions including design thinking, user-centred design, behaviour change theories, evaluation, and dissemination [46]. The framework recommends an intervention be pilot tested to assess preliminary efficacy, providing an opportunity to refine the study protocol prior to progressing to a definitive randomised controlled trial [46].

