### Randomisation

Participants will be randomly allocated by blocked randomisation to the intervention and wait-list control group using the Statistical Package for the Social Sciences (SPSS V.24). Due to the small sample size, blocked randomisation is deemed an appropriate technique for reducing the risk of bias and ensuring equal allocation between groups [20]. The wait-list control group will not be provided with any materials relating to the intervention or recommendations on how they can improve on their current lifestyle habits to maintain a ‘true control’. Upon the completion of data collection at 3 months, participants in the wait-list control group will be offered access to the intervention. The randomisation procedure will be carried out by a researcher not affiliated with the study. Participant allocation will be placed in a sealed envelope and opened by the lead researcher upon completion of baseline data collection.

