### Progression criteria

Progression to a definitive trial will be determined by the following progression criteria for participant recruitment, utilised previously in pilot and feasibility studies [11, 38].75-100% of the target sample size (30) recruited to the study will warrant progression to a definitive trial50-74% of the sample size (30) recruited to the study will warrant progression to a definitive trial following necessary adjustments to barriers of recruitment outlined during the process evaluation25-49% sample size (30) recruited to the study will only warrant progression to a definitive trial if changes to the protocol are made by both the research team and the potential future co-applicantsLess than 25% of the sample size (30) recruited to the study will indicate that the trial is unlikely to progress.

Progression criteria for retention rates will follow the criteria below [29]: > 80% retention rate will warrant progression to a definitive trial60-80% retention rate will warrant progression to definitive trial following necessary adjustments to counter attrition < 60% retention rate will indicate progression to a definitive trial is unlikely

Participant satisfaction will be assessed through the process evaluation and will provide information on whether the intervention was feasible, including the process of randomisation. Progression to a definitive trial will be dependent on acceptability, with necessary modifications indicated by the participants being made prior to progressing.

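### Repeated measures ANOVA uses the pre-allocation baseline as an outcome level and, in its classical form, discards men with one missed visit; a baseline-adjusted mixed model would use the same data better at no cost

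*Protocol article*

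**What the plan says.** Under Quantitative analysis the protocol article fixes one method for all efficacy outcomes: "Repeated measures ANOVA will be used to assess the preliminary efficacy between groups across three time points". The abstract's Methods paragraph defines the time points: "Outcomes will be assessed at baseline, 7 weeks, and 3 months after group allocation". Under Randomisation, the allocation envelope is "opened by the lead researcher upon completion of baseline data collection", so every baseline value precedes knowledge of the arm.

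The article does not say which ANOVA term (group, or group-by-time) is the efficacy contrast. It mentions neither baseline as a covariate nor the handling of missed visits.

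On size: "We have chosen a sample size of 30 for this study", and "no formal power calculation will be completed to determine sample size". On attrition, the Background states that "weaknesses of eHealth interventions include poor adherence and high rates of attrition" and reports 61% attrition in an earlier trial in taxi drivers. Under Progression criteria, more than 80% retention is the unconditional threshold. In the 60–80% band, the "retention rate will warrant progression to definitive trial following necessary adjustments to counter attrition".

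**The concern.** Baseline is measured before the arms differ, so in a randomised comparison its proper role is as a covariate. Entering it as one of three outcome levels has a price under either reading of the ANOVA. The group main effect averages in a visit at which the true difference is zero. The group-by-time term avoids that, but it uses baseline as a subtraction and not as a regression adjustment, which is less precise unless visits are very highly correlated.

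Separately, classical repeated measures ANOVA needs all three values from each man. Someone who attends at baseline and 3 months but misses 7 weeks, or attends at 7 weeks and then leaves, contributes nothing, although his follow-up value has been collected.

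At stake is the quality of the preliminary efficacy estimates. The article expects the study to inform a fully powered trial, so avoidable loss of precision, or a shrunken contrast, would be carried into that planning.

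**Working it through.** The plan gives no power, alpha, effect size or standard deviation, so there is no figure of its own to reproduce.

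**Inputs from the article:** 30 men; equal allocation, so about 15 per arm; visits at baseline, 7 weeks and 3 months; baseline before allocation.

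**Assumptions, not in the article:** unit variance; compound symmetry with between-visit correlation r from 0.3 to 0.8; the same true effect d at both follow-up visits.

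**1. Group main effect.** Its expectation is (0 + d + d)/3 = 0.67d. For a true effect of 0.80 SD this is 0.53 SD, and simulation also gave 0.53.

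**2. Group-by-time compared with baseline adjustment.** Take the mean of the two follow-up values, whose variance is (1+r)/2.
- Change from baseline: (1+r)/2 + 1 − 2r = 3(1−r)/2.
- Adjusted for baseline: (1+r)/2 − r² = (1−r)(1+2r)/2.
- Ratio, adjusted to change: (1+2r)/3.

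| r | adjusted | change | ratio |
|---|---|---|---|
| 0.3 | 0.56 | 1.05 | 0.53 |
| 0.5 | 0.50 | 0.75 | 0.67 |
| 0.6 | 0.44 | 0.60 | 0.73 |
| 0.7 | 0.36 | 0.45 | 0.80 |
| 0.8 | 0.26 | 0.30 | 0.87 |

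For r of 0.5–0.7, the change contrast needs 1/0.67 = 1.5 to 1/0.80 = 1.25 times as many men for the same precision.

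**3. Power, for illustration only** (15 per arm, complete data, true effect 0.8 SD, two-sided 5%, 5,000 simulated trials per setting).

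| r | group main effect | group-by-time F (2 df) | baseline-adjusted |
|---|---|---|---|
| 0.5 | 0.41 | 0.60 | 0.84 |
| 0.7 | 0.35 | 0.82 | 0.93 |
| 0.8 | 0.33 | 0.95 | 0.98 |

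With no true effect, all three tests rejected about 5% of the time.

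**4. Missed visits.** If each follow-up visit is missed independently with probability m, the number with both is 30(1−m)² and the number with at least one is 30(1−m²).
- m = 0.10: 24.3 against 29.7 men.
- m = 0.20: 19.2 against 28.8 men.

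Independent misses favour the mixed model. The opposite extreme is loss before 7 weeks, where a man has no follow-up value under either method. A simulation of both patterns (r = 0.6, effect 0.5 SD, 25% lost by 3 months, a further 10% missing 7 weeks at random, covariance treated as known) gave these standard errors in SD units:

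| Timing of loss | change contrast, men with all visits | baseline-adjusted, men with all visits | baseline-adjusted, all follow-up used |
|---|---|---|---|
| after 7 weeks | 0.35 | 0.31 | 0.26 |
| before 7 weeks | about 0.35 | 0.31 | 0.29–0.30 |

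Baseline adjustment accounts for about 0.04 SD of the gain whatever the timing. Using partial follow-up adds about 0.05 SD when men leave late and only 0.01–0.02 SD when they leave early. The article gives no information on timing.

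**The case against.** The strongest reply is about materiality. Efficacy is a secondary objective, the article says the trial is not powered and promises cautious interpretation, and the progression criteria concern recruitment, retention and acceptability. No decision rests on this ANOVA. That stands, and it limits the severity.

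Several stronger readings are tempting, and the article does not support them.
- **The effect will be diluted by a third.** This holds only if the group main effect is read. Group-by-time is at least as natural a reading, and it is undiluted.
- **ANOVA cuts 30 men to 18–24.** Those are 60% and 80% of 30. Men who leave before 7 weeks are lost to the mixed model too, so the whole shortfall cannot be charged to ANOVA.
- **The protocol accepts 60–80% retention.** It does not; that band permits progression only after changes to counter attrition.
- **Incomplete cases will be dropped, and only F-tests reported.** Neither is stated. The first is a property of the classical method, which a fuller document could modify. The second is reporting detail that an article may leave out.
- **The results will be seriously biased or produce false positives.** Type I error was about 5% in complete data. A simulation with roughly a quarter lost by 3 months gave 0.53 SD in men with all visits against a truth of 0.50. That gap is under a tenth of the 0.35 standard error.

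What the reply does not remove is the choice of method. It is stated positively, it makes a pre-allocation value an outcome level, and a better use of the same data is available in the same software.

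**Conclusion.** The point holds as a moderate one. The stated analysis is less precise than the collected data allow if group-by-time is read, and shrinks the follow-up difference to about two thirds if the group main effect is read. In its classical form it also sets aside the data of men with one follow-up visit.

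The firmest part is the gain from baseline adjustment: 67–80% of the variance of the change contrast for r of 0.5–0.7, and 53–87% over 0.3–0.8. This rests on compound symmetry, a similar effect at both follow-ups and an assumed correlation. The further gain from partial follow-up depends on when men leave and may be small. The feasibility conclusions are untouched; what improves is the efficacy estimates handed to the definitive trial.

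**What to change.** Under Quantitative analysis, replace repeated measures ANOVA with a linear mixed model for each continuous efficacy outcome (MIXED in SPSS V.24).
- **Response:** the 7-week and 3-month values.
- **Fixed effects:** arm, visit, arm-by-visit and the baseline value of that outcome.
- **Covariance:** unstructured over the two visits.
- **Participants:** every randomised man with any follow-up value, in the arm to which he was allocated.
- **Report:** the adjusted mean difference with its 95% confidence interval at each visit.

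The cost is a change of wording: same software, no new data, visits or participants. The model relies on data being missing at random and recovers little for men lost before 7 weeks, so the article should say so.
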